## Abstract

**Background:**

Cardiovascular diseases (CVDs) were accountable for 24% of the total deaths in Cambodia, one of the low- and middle-income countries, where primary health care (PHC) settings generally do not perform well in the early detection, diagnosis, and monitoring of leading risk factors for CVDs, that is, type 2 diabetes (T2D) and hypertension (HT). Integrated care for T2D and HT in the Cambodian PHC system remains limited, with more than two-thirds of the population never having had their blood glucose measured and more than half of the population with T2D having not received treatment, with only few of them achieving recommended treatment targets. With regard to care for T2D and HT in the public health care system, 3 care models are being scaled up, including (1) a hospital-based model, (2) a health center–based model, and (3) a community-based model. These 3 care models are implemented in isolation with relatively little interaction between each other. The question arises as to what extent the 3 care models have performed in providing care to patients with T2D or HT or both in Cambodia.

**Objective:**

This protocol aims to show how to use primary data from a population-based survey to generate data for the cascades of care to assess the continuum of care for T2D and HT across different care models.

**Methods:**

We adapt the HIV test-treat-retain cascade of care to assess the continuum of care for patients living with T2D and HT. The cascade-of-care approach outlines the sequential steps in long-term care: testing, diagnosis, linkage with care, retention in care, adherence to treatment, and reaching treatment targets. Five operational districts (ODs) in different provinces will be purposefully selected out of 103 ODs across the country. The population-based survey will follow a multistage stratified random cluster sampling, with expected recruitment of 5280 eligible individuals aged 40 and over as the total sample size. Data collection process will follow the STEPS (STEPwise approach to NCD risk factor surveillance) survey approach, with modification of the sequence of the steps to adapt the data collection to the study context. Data collection involves 3 main steps: (1) structured interviews with questionnaires, (2) anthropometric measurements, and (3) biochemical measurements.

**Results:**

As of December 2021, the recruitment process was completed, with 5072 eligible individuals participating in the data collection; however, data analysis is pending. Results are expected to be fully available in mid-2022.

**Conclusions:**

The cascade of care will allow us to identify leakages in the system as well as the unmet need for care. Identifying gaps in the health system is vital to improve efficiency and effectiveness of its performance. This study protocol and its expected results will help implementers and policy makers to assess scale-up and adapt strategies for T2D and HT care in Cambodia.

**Trial Registration:**

International Standard Randomised Controlled Trials Number (ISRCTN) registry ISRCTN41932064; https://www.isrctn.com/ISRCTN41932064

**International Registered Report Identifier (IRRID):**

DERR1-10.2196/36747

## Introduction

Globally, cardiovascular diseases (CVDs) are responsible for the death of 17.9 million people annually, accounting for 31% of all deaths [1]. More than 75% of deaths attributable to CVDs occur in low- and middle-income countries (LMICs), where primary health care (PHC) settings generally do not perform well in the early detection, diagnosis, and monitoring of type 2 diabetes (T2D) and hypertension (HT), which are the leading risk factors for CVDs [1,2]. In regions where early diagnosis and care are not available or inadequate, T2D and HT-related complications—including CVDs, kidney disease, neuropathy, blindness, and lower-extremity amputation—are a significant cause of morbidity and mortality among people with T2D or HT or both [3,4]. The resulting complications will increase health care costs and pose challenges to population health, socioeconomic development, and health systems [5,6], negatively affecting country’s effort to achieve universal health coverage [7]. Globally, adult populations with HT and T2D had increased from 594 million to 1.13 billion between 1975 and 2015 [8] and from 4.7% to 8.5% between 1980 and 2014 (with approximately 422 million living with T2D in 2014), respectively [2]. Access to a lifelong continuum of care is therefore critical for those living with T2D or HT or both as well as for the prevention of CVDs [9]. The World Health Organization Package of Essential Noncommunicable Disease Interventions (WHO PEN) offers substantial international support for PHC services to include care for T2D and HT in LMICs [10].

In Cambodia, CVDs were estimated to account for 24% of the total deaths in 2018 [11], and in 2016 the prevalence rates of T2D and HT were 9.6% and 14.2%, respectively, among adult population between the ages of 18 and 69 years [12]. This seems a significant increase, as the prevalence of T2D between ages 25 and 64 was only 2.9% in 2010 [12]. However, integrated care for T2D and HT in the Cambodian PHC system remains limited [13]. More than two-thirds of the population have never had their blood glucose measured, and more than half of the population with T2D is not receiving treatment [12,14]. The proportion of patients with T2D accessing treatment is low, with few achieving recommended treatment targets [15].

The response to these T2D and HT epidemics requires concerted effort from both global health governance and Cambodia’s health system. Cambodia has a pluralistic health system, with a public health care system operated by the Ministry of Health, complemented by many private health care services that mainly offer outpatient curative care, operating largely without sufficient steering and coordination from the government [16]. The government’s public health care system was established based on a district health system model, following the PHC approach. With regard to the care for T2D and HT in the public health care system, the following 3 care models are being scaled up: (1) a *hospital-based model*, (2) a *health center–based model*, and (3) a *community-based model*.

The hospital-based model is a standard care model for T2D and HT that is available at district or provincial referral hospitals as part of outpatient consultation. These referral hospitals provide ambulatory care and support the health centers in treating serious cases. Health centers are allowed to take care of mild or stable cases without complications. The referral hospitals will treat serious cases [13]. In 2018, the Ministry of Health added a second component to this standard care: 29 district and provincial referral hospitals (out of 117) provided exclusive health care services for patients with T2D or HT or both in a separate section, giving explicit attention to these conditions [17].

The health center–based model has been given increasing attention by the Ministry of Health with support from the World Health Organization through the adoption of the WHO PEN for PHC [10]. The National Standard Operating Procedure for T2D and HT Management in Primary Care was developed out of the WHO PEN and approved in 2019 to strengthen implementation of the integrated basic care for T2D and HT in the PHC system. In this health center–based model, health center staff are trained to do screening, provide follow-up care for patients with T2D or HT or both with mild and stable conditions (with diagnosis only undertaken at the referral hospital), and offer health education and counseling on healthy behavior as part of screening for CVD risk factors [13]. With mild HT cases, health center staff are allowed to initiate treatment. At the health center level, care for both T2D and HT is described in a national clinical guideline on the minimum package of activities specified for health centers [18]. Yet, in practice, implementation of this guideline is not as complete as intended because the public health care system has not yet been substantially reoriented from primarily addressing acute health needs toward continuing care for chronic conditions. The public health system currently focuses on communicable diseases (HIV and AIDS, tuberculosis, malaria, diarrhea, and respiratory diseases) and maternal and child health [19]. In early 2020, only 86 health centers (out of 1221) implemented the WHO PEN program since its pilot in 2015 [17].

The community-based model is predominantly run by a Cambodian nongovernmental organization called MoPoTsyo that operates Peer Educator Networks with 4 main key services for patients with T2D or HT or both. These services include (1) self-management training through peer educator visits, (2) laboratory tests, (3) physician consultations, and (4) low-cost medicines delivered through a revolving drug fund program to the members in the network in 8 out of 24 provinces across the country. By 2019, 255 peer educators have been trained to serve over 40,000 patients [20]. In this community-based model, peer educators, who are patients with T2D or HT or both themselves, have been trained by MoPoTsyo to be educators and counselors on lifestyle change. Peer educators also assist registered patients in the networks to have access to professional medical consultations at the public referral hospitals with which they have partnership agreements [20].

These 3 care models are implemented in isolation with relatively little interaction between each other. There have been few empirical studies on their performance. The question arises as to what extent the 3 care models have performed in providing care to people with T2D or HT or both in Cambodia. Care models that are integrated in terms of shared information and resource coordination have shown to be effective and efficient in many contexts [21]; however, implementation and scale-up of effective care models for T2D and HT remain limited, especially in LMICs. How well different models perform in contributing to good health outcomes is also not well documented. The outcomes of chronic care are difficult to measure, as such care does not have a clear end point, but requires comprehensive illness management along a continuum of care, from detection and diagnosis for initiating treatment and follow-up to successful management of the illness. This complexity requires a comprehensive framework of measurement to assess the performance of care for T2D and HT.

Inspired by noticeable successes in providing the continuum of care to people living with HIV in Cambodia [22], we adapted the HIV test-treat-retain cascade of care [23] in this study protocol to assess the continuum of care for patients living with T2D or HT or both. This method documents how many patients are lost to follow-up between the stages of testing and diagnosis, linkage with and retention in care, and adherence to treatment and control of health conditions. The cascade-of-care approach outlines the aforementioned sequential steps in long-term care. Recently, this approach has been applied to T2D and HT by pooling secondary data from cross-sectional studies of nationally representative surveys in LMICs [24,25]. This was used to produce cascades of care as an approach to assess the performance of health systems to meet the continuum of care for patients living with T2D or HT or both. Two studies, one in the United States and the other in South Africa, developed and field tested the cascade of care for T2D and HT [26,27]. Their analysis was mainly based on extracted secondary data from broader nationally representative surveys, not specifically designed for this purpose.

Given that Cambodia implements T2D and HT services through 3 different care models, we propose the cascade-of-care approach to assess the performance of these care models along the continuum of care. We will do so using primary data collection. This study protocol aims to serve as a tool to generate the cascades of care for T2D and HT for the 3 care models using the primary data of a population-based survey. The specific aims are as follows:

To generate the cascades of care for T2D for (1) hospital-based care, (2) health center–based care (WHO PEN), (3) community-based care (Peer Educator Network), and (4) coexistence of 1, 2, and 3;To generate the cascades of care for HT for (1) hospital-based care, (2) health center–based care (WHO PEN), (3) community-based care (Peer Educator Network), and (4) coexistence of 1, 2, and 3;To compare the cascades of care for T2D between the care models 1-4;To compare the cascades of care for HT between the care models 1-4.

## Methods

### Study Design

This study protocol is part of a larger population-based survey—the SCUBY (Scale up diabetes and hypertension care for vulnerable people in Cambodia, Slovenia and Belgium) project [28], which includes other substudies focusing on (1) the health status of people aged 40 and over and the existence of comorbidities, (2) health care utilization and health care expenditure among people aged 40 and above and people living with T2D or HT or both, (3) the lifestyle and knowledge of T2D and HT among people living with T2D or HT or both, and (4) the self-management and social support for people living with T2D or HT or both.

To meet the aforesaid specific aims, 5 operational districts (ODs) in different provinces will be purposefully selected out of 103 ODs across the country. The selection is based on a mapping exercise conducted in the SCUBY project. Only in the OD Daunkeo the 3 care models coexist. The OD Samrong in a bordering province hosts a typical noncommunicable disease (NCD) clinic at the referral hospital (the WHO PEN and Peer Educator Network are not there yet). The OD Kong Pisey does not have the WHO PEN and the NCD clinic at the referral hospital (only the Peer Educator Network of MoPoTsyo exists—with relatively strong network). The OD Pearaing is one of the ODs piloting the WHO PEN and started implementing the program since 2015. At the time of study, 8 of 9 health centers have implemented the WHO PEN. The OD Sotr Nikum is historically and significantly influenced by the financial aid of various development partners and nongovernmental organizations—contextual factor is a focus. The referral hospital in this OD has a Chronic Disease Clinic, where people with T2D or HT or both and those with HIV seek treatment and care [29]. At the time of study, 5 of 25 health centers have implemented the WHO PEN. Table 1 shows the existence of care provision for T2D and HT in each OD.

**Table 1 table1:** Selected provinces and ODs^a^ with different types of care models.

OD name	Province	Existing care provision	Care model
Samrong	Oddar Meanchey	NCD^b^ clinic at the referral hospital	Hospital-based care
Pearaing	Prey Veng	NCD clinic^c^ + WHO PEN^d^ (high coverage)	Health center–based care
Sotr Nikum	Siem Reap	NCD clinic^c^ + WHO PEN (low coverage)	Health center–based care with context
Kong Pisey	Kampong Speu	Peer Educator Network^e^	Community-based care
Daunkeo	Takeo	NCD clinic + WHO PEN + Peer Educator Network	Coexistence of care

^a^OD: operational district.

^b^NCD: noncommunicable disease.

^c^In the WHO PEN implementation arrangement, the referral hospital in the OD supports the health centers in providing the secondary care.

^d^WHO PEN: World Health Organization Package of Essential Noncommunicable Disease Interventions.

^e^The Peer Educator Network arranges a medical consultation for their registered patients once a week at the referral hospital in the OD.

This population-based survey includes 2 questionnaires (Multimedia Appendices 1 and 2). One questionnaire is directed at household heads and inquires about the household’s socioeconomic status, member characteristics, general health of the household members, and their access to health care and health-related expenditure. The other questionnaire is for eligible adults (ie, adults aged ≥40) of the selected households and inquires about their sociodemographic information, health status and comorbidity, quality of life, health care utilization, social support, behavioral measurements, and knowledge of T2D and HT for known patients with T2D or HT or both in particular. Known patients with T2D or HT or both are also asked about their medical adherence and decision-making power over diet.

### Sampling and Sample Size

This population-based survey follows a multistage stratified random cluster sampling [30]. For the sampling procedure, each OD is considered as a stratum due to the care model present (Table 1). Based on rules of stratification, each stratum is theoretically independent from one another, and its selection can be based on the aforementioned specific aims [30]. In each stratum, clusters of primary sampling units (villages) will be randomly sampled.

Based on the multistage stratified random cluster sampling, 3 stages of stratification are applied, and in each stage randomization is employed. ODs are the strata, and health centers impacted by the types of care models are selected. For the first stage of stratification, sampling with equal probability (equal probability selection method) will be used to determine the number of villages under the catchment areas of the impacted health centers in each OD. This equal selection is also made to ensure oversampling for some ODs. If using proportionate allocation of the sample units across the ODs, the sample selected from the ODs representing certain types of care models would be too low to have enough statistical power for the analyses. In this survey, disproportionate allocation is done to randomly select equal-sized samples in the 5 ODs [30]. For the second stage of stratification, households having adult(s) aged 40 and above (secondary sampling units) in the selected villages are selected and listed. Systematic random sampling is used to select the households from each village. For the third stage of stratification, only 1 individual meeting the eligibility criteria (described later) is randomly selected from each household to reduce the clustering effect. Thus, 1 eligible individual is selected from each household, making the total sample size of eligible individuals the same as the sample size of households (Figure 1).

**Figure 1 figure1:**
[figure not shown]
Flow of the sampling frame.

The sample size of households in all the selected 5 ODs is calculated based on the following formula [30]:

n_h_ = (z^2^)(r)(1–r)(f)(k)/(p)(*γ*)(e^2^)

where n_h_ is the parameter to be calculated and the sample size in terms of the number of households to be selected; z is the statistic that defines the level of confidence desired (1.96 for the 95% level of confidence); r is an estimate of a key indicator to be measured by the survey (the key indicator being T2D prevalence—this r being 0.1 according to 10% of T2D prevalence among adults aged 40 and over—the national STEPS survey 2016 [12]); f is the sample design effect (1.5 used in accordance with the national STEPS survey 2016 [12] and the Cambodian demography and health survey 2014 [19]); k is a multiplier to account for the anticipated rate of nonresponse (1.2 for 20% anticipated rate, as used in the national STEPS survey 2016 [12]); p is the proportion of the total population accounted for by the target population and upon which the parameter r is based (0.24 for 24% [31]); *γ* is the average household size (4.6 for the number of persons per household in the selected provinces—census 2019 [32]); and e is the margin of error to be attained (0.01 for the level of precision at 10% of r).

While HT prevalence is higher, T2D prevalence of 10% [12] is used as the main key indicator of interest to determine the sample size, which is important for the cascade of care. Based on the aforementioned formula, the total sample size would be 5637 households, including 20% of anticipated nonresponse rate. Enlarging the sample size to include enough patients to assure significant differences for the detection of the number of patients with T2D having blood glucose under control would increase the budget 5-fold, which is not feasible. Taking feasibility and budget constraint into consideration, a fixed cluster size of 24 households per village, with 44 villages randomly selected in each OD, will be applied for the sake of controlling the total sample size and interviewer workloads [30]. Thus, a cluster size of 24 households per village over the total villages of 220 would yield the total sample size of 5280 households (also equal 5280 eligible individuals).

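### The 5637-household figure is mis-derived (divisor 1.104 where one adult is interviewed per eligible household; 1.2 for 20% nonresponse), and its ±1-point precision is pooled while the aims are by care model

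*Protocol article*

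**What the plan says.** Methods, Sampling and Sample Size, gives a household formula, n = z² r(1−r) f k / (p γ e²), applied to all five selected ODs together. The inputs are all printed: "z is the statistic that defines the level of confidence desired (1.96 for the 95% level of confidence"; "this r being 0.1 according to 10% of T2D prevalence among adults aged 40 and over"; "f is the sample design effect (1.5 used in accordance with the national STEPS survey 2016"; and "k is a multiplier to account for the anticipated rate of nonresponse (1.2 for 20% anticipated rate". In addition p = 0.24 (share of the population in the target age group), γ = 4.6 (persons per household) and e = 0.01, described as 10% of r. The result is that "the total sample size would be 5637 households, including 20% of anticipated nonresponse rate".

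For feasibility and budget, the article then fixes 24 households in each of 44 villages in each of five ODs, which "would yield the total sample size of 5280 households (also equal 5280 eligible individuals").

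On the sampling itself, the same section says that "1 eligible individual is selected from each household, making the total sample size of eligible individuals the same as the sample size of households". Target Population and Recruitment Strategy adds that the household list contains only households with at least one adult aged 40 or over, that people who cannot be reached after callbacks are replaced by the next listed household, and that those who refuse are dropped.

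The four specific aims at the end of the Introduction are cascades for diabetes and hypertension by care model, and comparisons between models. Results reports 5072 participants.

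**The concern.** The formula and the sampling scheme describe two different surveys. Dividing by p × γ suits a survey that visits average households and interviews everyone of eligible age in them. Here households without an eligible adult are removed beforehand and one person is taken from each of the rest, so a responding household yields exactly one interview. The nonresponse multiplier is also too small for the rate it is said to cover.

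Separately, the only precision target in the article concerns one prevalence over five purposively chosen ODs. The aims are answered within and between care models, and every cascade bar after the first is a proportion of people with the disease. Someone who takes ±1 point, or 10% of r, as the precision of the study's answers would be misled about what the diabetes comparisons can show.

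**Working it through.** **Inputs** (all from Sampling and Sample Size unless noted): z = 1.96, r = 0.10, f = 1.5, k = 1.2, p = 0.24, γ = 4.6, e = 0.01; 5280 households planned, 1056 per OD; 5072 participants achieved (Results), or 1014 per OD if spread evenly.

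**Step 1. The stated figure.** 1.96² × 0.1 × 0.9 × 1.5 × 1.2 / (0.24 × 4.6 × 0.01²) = 5637.1. This matches 5637, so there is no slip in the calculation. The figure rests on the divisor 0.24 × 4.6 = 1.104 and on k = 1.2.

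**Step 2. Completed interviews needed.** 1.96² × 0.1 × 0.9 × 1.5 / 0.01² = 5186.2, so 5187.

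**Step 3. Households at one interview each.**
- k = 1.2: 5186.2 × 1.2 = 6223.4, so 6224.
- 20% loss made good in full: 5186.2 / (1 − 0.20) = 6482.7, so 6483.
- Check on k: 1.2 × 0.8 = 0.96, so 1.2 leaves a 4% deficit at 20% loss. It covers 1 − 1/1.2 = 16.7%.

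Against 6224 and 6483, the stated 5637 is 9% and 13% short, and 5280 is 15% and 19% short. Against 5637 itself, 5280 appears only 6% short. These household counts assume that no loss is replaced.

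**Step 4. Pooled margin attained**, 1.96 × √(0.1 × 0.9 × 1.5 / n):

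| Completed interviews | Margin (points) |
|---|---|
| 5280 | ±0.99 |
| 5072 (achieved) | ±1.01 |
| 4224 (5280 less 20%, none replaced) | ±1.11 |

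**Step 5. Prevalence margin per OD**, same formula: n = 1056 gives ±2.22 points and n = 1014 gives ±2.26. That is 22 to 23% of r, not 10%.

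**Step 6. Diabetes bars per OD.** Cases: 0.10 × 1056 ≈ 106, or 0.10 × 1014 ≈ 101. For a bar at 50% (an assumption; the article gives no expected bar heights), 1.96 × √(0.25 × f / cases):
- f = 1: ±9.5 points (106 cases) to ±9.7 (101 cases).
- f = 1.5: ±11.7 to ±11.9.

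**Step 7. Two-OD contrast, about 101 cases each, 80% power, two-sided 5%.** The detectable difference is about (1.96 + 0.84) × √(2 p̄(1 − p̄) f / 101). Starting from 30%, f = 1 gives p̄ ≈ 0.40 and 2.80 × √(2 × 0.24 / 101) ≈ 0.19. With f = 1.5, p̄ ≈ 0.42 and 2.80 × √(2 × 0.243 × 1.5 / 101) ≈ 0.24. So about 19 points, up to 24. For an assumed 30% against 40%, power is about 0.32 (f = 1) or 0.23 (f = 1.5).

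**Step 8. Which value of f within cases?** If all of f = 1.5 came from clustering at 24 people per village, the intraclass correlation would be 0.5/23 ≈ 0.022. With about 2.4 cases per village the design effect would be 1 + 1.4 × 0.022 ≈ 1.03. The lower figures in Steps 6 and 7 are then the better supported. Weighting, or stronger clustering of care outcomes, could raise them, but the article gives no figure for either.

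**The case against.** The strongest reply is that little follows for the pooled figure. 5637 was never the fielded size, the article openly fixes 5280 on budget grounds, and 5280 completes would meet the ±1-point target. The achieved 5072 miss it by 0.01 of a point. This stands, and it limits the divisor and the multiplier to errors in a stated derivation.

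Several stronger readings are tempting, and the article does not support them.

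- *That 5280 assumes complete response.* Non-contacts are replaced and only refusals are dropped, so 4224 interviews is a worst case. The achieved shortfall is 1 − 5072/5280 = 3.9%; at that loss, 5187 completes would need about 5400 households, not 6483. What stands is that the article never says how replacement and the multiplier fit together.
- *That the article promises adequate power per OD and then retracts it.* It says that, under proportionate allocation, the sample from some ODs "would be too low to have enough statistical power for the analyses". It does not say that equal allocation achieves enough power, so this does not contradict the later admission about glucose control.
- *That prevalence is irrelevant to the aims.* It is bar 1 of each cascade and defines the fixed denominator, and Statistical Analysis Plan lists it as a regression outcome. The mismatch lies in pooling it.
- *That every model has only about 101 cases.* Table 1 has two health center-based ODs. Combined, they would have about 2 × 101 ≈ 203 cases and a margin of 1.96 × √(0.25/203) ≈ ±6.9 points for a 50% bar (f = 1).
- *That non-significance will be taken as equal performance.* Nothing in the article says so; it is only a risk for readers.

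The article also discloses that sizing for differences in glucose control would need a five-fold budget. That disclosure names one bar. It gives no per-OD precision and does not mention the other diabetes bars.

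**Conclusion.** The point holds in two parts. First, the printed derivation of 5637 is wrong for the design described: the divisor should be 1 rather than 1.104, and 20% loss needs 1.25 rather than 1.2. This follows from the article alone. Its effect on attained pooled precision is negligible (±1.01 points from 5072).

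Second, and of more consequence, the only stated precision is at a level that aims 1-4 do not use. On the article's own r and f, an OD has a prevalence margin a little over twice the stated one, and a single-OD diabetes bar near 50% is known to about ±10 points (±12 if f = 1.5 also held among cases). A two-OD contrast has 80% power only for about 19 points, up to 24. These subgroup figures assume 10% prevalence in each OD, an even spread of participants and the illustrative bar heights. Hypertension is not quantified here: the article calls it more prevalent but gives no prevalence for age 40 and over, so those cascades would be more precise by an amount that cannot be computed.

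**What to change.** In Sampling and Sample Size:

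1. Restate the derivation with one interview per listed eligible household (divisor 1) and k = 1/(1 − 0.20) = 1.25, and say how replacing non-contacts enters, since it lowers the number of households needed.
2. Keep the budget explanation for 5280, and give the attained precision beside it: pooled prevalence about ±1.0 point; per OD about ±2.3 points for prevalence and about ±10 to 12 points for a diabetes bar near 50%, with the assumed bar height and design effect stated. Say whether the two health center-based ODs are analysed together or apart.
3. Extend the limitation now given only for glucose control to the diabetes comparisons between models as a whole. Report these as differences with confidence intervals alongside the detectable difference. One sentence that a non-significant difference is not evidence of equal performance would forestall that misreading.

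The cost is rewording. No recruitment, data collection or weighting changes; the stated precision becomes less favourable.
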